### Blinding assessment

The acupuncturists will ask participants to guess whether they received acupuncture treatment or sham acupuncture after the last treatment in week 4.

### Sample size

The study uses the HAMD-17 as the primary outcome measure for sample size calculation. The sample size was calculated using the following formula for the comparison of two samples:
$$ n=\frac{{\left({Z}_{1-\frac{a}{2}}+{Z}_{1-\beta}\right)}^2\times \left({\sigma}_1^2+{\sigma}_2^2\right)}{\delta^2} $$

In this study, a two-tailed test was chosen; σ_1_ and σ_1_ represent the difference in the change in HAMD-17 scores after treatment in the test group (acupuncture group) and placebo group (control group), respectively, and δ represents the difference between the two groups. Power Analysis and Sample Size software (PASS; version 11; NCSS Statistical Software, Kaysville, UT, USA) was used for sample size calculation. According to the results of a pilot study [26], σ_1_=9.50, σ_2_=7.42, δ=2.08, *α*=0.05, $$ {Z}_{1-\frac{a}{2}} $$=1.96, *β*=0.1, and *Z*_1 − *β*_=1.28. The calculated sample size of each group was approximately 22 individuals to achieve a power of 0.90 at a significance level of 0.05. After accounting for an anticipated dropout rate of 20%, the total number of patients required for this trial was 56, with 28 in each group.

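### The sample size of 22 per group does not follow from its own formula and inputs (these give 353), and the values entered as standard deviations appear to be the two arms' mean changes

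*Protocol article*

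**What the plan says.** All of the material is in the Sample size section of the protocol article.

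- **Formula.** "The sample size was calculated using the following formula for the comparison of two samples": n per group = (Z₁₋α/₂ + Z₁₋β)² × (σ₁² + σ₂²) / δ². In this formula σ₁ and σ₂ have to be standard deviations.
- **Design values.** "a two-tailed test was chosen", "at a significance level of 0.05" (Z = 1.96) and "to achieve a power of 0.90" (Z = 1.28).
- **Inputs, credited to a pilot study.** "σ_1_=9.50, σ_2_=7.42, δ=2.08".
- **Definitions.** The sigmas "represent the difference in the change in HAMD-17 scores after treatment in the test group (acupuncture group) and placebo group (control group), respectively". Delta is defined as the contrast between the arms.
- **Result.** "The calculated sample size of each group was approximately 22 individuals to achieve a power of 0.90 at a significance level of 0.05". An allowance for 20% dropout then raises this to 28 per group, 56 in total.

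The article gives no other SD for HAMD-17 or its change.

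**The concern.** The article publishes a complete worked calculation (formula, inputs and answer), and the answer does not follow from the inputs. The definitions add to the doubt: each sigma is described as a change in score in one arm rather than as the spread of that change, and delta equals the first sigma minus the second.

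This calculation is the only justification given for recruiting 56 patients to a superiority trial. The spread of the HAMD-17 change determines its power, and that spread is never stated. If the true SD is well above the value that 22 per group implies, the trial has far less than 90% power for the effect it names. A non-significant result would then say little about whether that effect exists, while the protocol would present it as coming from a well-powered trial.

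**Working it through.** **1. The plan's own figure.** All inputs come from the Sample size section.

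- (1.96 + 1.28)² = 3.24² = 10.4976
- σ₁² + σ₂² = 9.50² + 7.42² = 90.25 + 55.0564 = 145.3064
- δ² = 2.08² = 4.3264
- n = 10.4976 × 145.3064 / 4.3264 = 352.6, so **353 per group**, against the stated 22 (352.6 / 22 ≈ 16)

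**2. Other readings of the same inputs.** None gives 22.

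| Reading | n per group |
|---|---|
| One-sided, 90% power | 288 |
| Two-sided, 80% power | 264 |
| One-sided, 80% power | 208 |
| Sigmas taken as variances, two-sided 90% | 41.1 |
| Sigmas taken as variances, two-sided 80% | 30.7 |
| Sigmas taken as variances, one-sided 90% | 33.5 |
| Sigmas taken as variances, one-sided 80% | 24.2 (25 after rounding up) |

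**3. The dropout step.** 22 / (1 − 0.20) = 27.5, rounded up to 28 per group and 56 in total. This step is correct, so the fault lies in the step that produces 22.

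**4. Where the inputs seem to come from.** 9.50 − 7.42 = 2.08, which is delta exactly. On the article's own definitions (a change in each arm, and the difference between arms), 9.50 and 7.42 read as mean changes and 2.08 as their difference.

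**5. Power if the printed values really were SDs.** This checks the printed claim only.

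- 22 per group: SE = √(145.3064 / 22) = 2.570; δ/SE = 0.809; power = Φ(0.809 − 1.96) + Φ(−0.809 − 1.96) = 0.125 + 0.003 = 12.8%
- 28 per group: SE = √(145.3064 / 28) = 2.278; δ/SE = 0.913; power = 0.148 + 0.002 = 15.0%
- 353 per group after 20% dropout: 353 / 0.8 = 441.25, so 442 per group

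**6. The SD that 22 per group implies.** Solving the formula for a common SD at n = 22:

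- SD = √(22 × 4.3264 / (2 × 10.4976)) = 2.13 points
- By the t-test, SD 2.13 gives 88.6% power and SD 2.08 gives 90.0%

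The stated n therefore requires an SD of change of about 2.1 points, a standardised difference of about 1.0.

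**7. Power if 9.50 and 7.42 are means.** The SD is not given, so its range is an assumption. Delta is 2.08, two-sided alpha 0.05. Power is from the two-sample t-test. The last column uses the normal approximation, n = (1.96 + 1.28)² × 2 × SD² / 2.08².

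| Assumed SD of change | Power, 22 per group | Power, 28 per group | n per group for 90% |
|---|---|---|---|
| 3 | 61% | 72% | 44 |
| 4 | 39% | 48% | 78 |
| 5 | 27% | 33% | 122 |
| 6 | 20% | 25% | 175 |

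**8. Difference detectable with 90% power (t-test).** 1.00 SD of change with 22 per group; 0.88 SD with 28 per group.

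**The case against.** The strongest reply is that the software may have been run correctly and the inputs misprinted. A t-test at a standardised difference of 1.0 (SD 2.08) has 89.97% power with 22 per group, which matches the stated answer closely. In that case this would be a reporting error, and 56 patients would be adequate for the SDs actually used. That possibility stands: the article does not prove 22 wrong under every SD. It does not rescue the published calculation, because the article would then still print the wrong quantities as sigmas and omit the ones that matter.

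Two further objections have merit. First, the pilot study is not at hand, so reading 9.50 and 7.42 as mean changes is an inference. It is strongly supported by the exact subtraction and by the article's definitions, but it needs confirming. If it is right, the 353 per group and the 13% to 15% power describe no real scenario; they show only that the calculation fails and should not be quoted as the trial's power.

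Second, the Statistical analysis section plans an intention-to-treat analysis with last observation carried forward, so up to 28 per group may be analysed. Using 22 follows the plan's own dropout allowance. Using 28 is an upper bound, since carried-forward baseline values may dilute the effect. At 28 per group, power for SDs of 3 to 6 is still only 72% down to 25%.

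**Conclusion.** The concern holds. The stated 22 per group cannot be reproduced: the printed formula and inputs give 353. This depends on nothing outside the Sample size section.

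The claim of 90% power for a 2.08-point difference is unsupported, because it requires an SD of change of about 2.1 points that the article neither states nor defends. If the SD lies between 3 and 6 points (an assumed range), power is 61% down to 20% with 22 completers per group. The trial's actual power cannot be stated until the pilot's SDs of change are known. This must be corrected, because the size of the trial and its primary-outcome power claim both rest on it.

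**What to change.** 1. Check 9.50 and 7.42 against the pilot study. If they are mean changes, label them so and keep 2.08 as their difference.
2. Enter the pilot's SDs of HAMD-17 change as σ₁ and σ₂, describe them as standard deviations, and recompute n and power. Correct the repeated σ₁ in the definition at the same time.
3. If 56 patients is fixed, keep it. Unless the pilot SDs support the 90% claim, replace it with the power that 22 completers per group gives at those SDs, and show 28 per group beside it as the upper bound. Alternatively, state the difference detectable with 90% power: about 1.0 SD of change with 22 per group, 0.88 SD with 28.
4. Report the primary result with its confidence interval, and read it against that detectable difference.

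The cost is one recalculation and a change of protocol wording. The stated power will probably be less favourable, unless the pilot's SD turns out to be near 2.1. No extra patients are needed and trial conduct does not change.

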### Statistical analysis

Descriptive statistics will be used to describe demographic data of sample groups, while the normality of the distribution of each parameter will be checked by histogram and the Kolmogorov-Smirnov test. The continuous variables will be presented in mean and standard deviation (SD). A chi-squared test will be used to assess sample characteristics and gender. The data that conform to normal distribution will be analyzed by one-way analysis of variance, while the nonconforming data will be analyzed by Mann-Whitney *U* test. The latency and amplitude of the ERP data will be analyzed by mixed-effect model analysis, the Greenhouse-Geisser adjustment will be applied to adjust the degrees of freedom if the assumption of Mauchly’s test of sphericity is not significant. *P* < 0.05 will be taken as the standard for a significant difference. Data analysis will follow the intention-to-treat principle including participants who are randomly assigned. Missing data will be input with the last observation carried forward method.

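### The 20% dropout allowance assumes dropouts leave the analysis, but the plan keeps them with carried-forward values, so the stated 90% power does not describe the specified analysis

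*Protocol article*

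**What the plan says.** The Sample size section states the base result: "The calculated sample size of each group was approximately 22 individuals to achieve a power of 0.90". It then adds the allowance: "After accounting for an anticipated dropout rate of 20%, the total number of patients required for this trial was 56", that is, 28 per group.

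The Statistical analysis section fixes the analysis set: "Data analysis will follow the intention-to-treat principle including participants who are randomly assigned". It also fixes the handling of gaps: "Missing data will be input with the last observation carried forward method". The Data collection methods section agrees that the data of people lost to follow-up stay in the analysis.

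The Outcome measures section lists three assessment times: baseline, week 4 and week 8. The primary outcome is the change in HAMD-17 at week 4, and no visit falls between baseline and week 4.

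**The concern.** The allowance and the analysis treat the same people differently. Dividing by (1 − 0.20) supposes that dropouts contribute nothing and that about 22 completers per group are compared at the full difference. Under the specified analysis all 28 per group are compared. For someone lost before week 4 the last observation is the baseline score, so the change is zero by construction.

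Zeros in both arms pull the group difference towards nil. They also alter the spread, in a direction that depends on how large the real changes are. The claim that the trial is sized "to achieve a power of 0.90 at a significance level of 0.05" therefore refers to a different analysis from the one planned. A null HAMD-17 result could then be read as stronger evidence of no effect than it is.

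**Working it through.** **Inputs.** From Sample size: two-sided α = 0.05, z values 1.96 and 1.28, 22 per group for 90% power, 20% dropout, 28 per group, and "σ_1_=9.50, σ_2_=7.42, δ=2.08". From Outcome measures and Statistical analysis: no visit between baseline and week 4, all randomised participants analysed, LOCF.

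**1. The plan's own figures.**
- Dropout step: 22/0.8 = 27.5, rounded to 28. This reproduces. (22 × 1.2 = 26.4 would give 27.)
- Base step: (1.96 + 1.28)² × (9.50² + 7.42²)/2.08² = 10.50 × 145.31/4.326 ≈ 352.6, so 353 per group. The stated 22 does not reproduce. On the printed SDs, power is about 12% at 22 per group and 15% at 28, before any dropout.
- 9.50 − 7.42 = 2.08 exactly, so the two printed sigmas look like mean changes. In that case the article gives no usable SD.

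**2. Isolating the dropout step.** Take 22 per group at 90% as given. The implied standardised difference is 3.24 × √(2/22) = 0.977, and the implied SD is 2.08/0.977 = 2.13. This SD is inferred.

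**3. Effect of carrying baseline forward.** Let a fraction q of each arm be lost before week 4, and let m be an arm's mean change among completers.
- Expected difference: (1 − q) × 2.08. At q = 0.20 this is 0.8 × 2.08 = 1.66.
- Variance in an arm: (1 − q) × SD² + q(1 − q) × m². At q = 0.20 this is 0.8 × SD² + 0.16 × m².

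For mean changes of 9.50 and 7.42 the arm variances are 3.63 + 14.44 = 18.07 and 3.63 + 8.81 = 12.44, so the pooled SD is about 3.9.

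**4. Power at 28 per group** (normal approximation, then noncentral t):

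| Case | Difference | SD | Normal | t |
|---|---|---|---|---|
| No dropout | 2.08 | 2.13 | 95.5% | 94.8% |
| 20% leave the analysis (22.4 analysed) | 2.08 | 2.13 | 90.5% | 89.2% |
| 20% at zero change, SD held constant | 1.66 | 2.13 | 83% | 82% |
| 20% at zero change, mean changes 9.50 and 7.42 | 1.66 | 3.9 | 36% | 35% |
| 20% at zero change, mean changes 2.08 and 0 | 1.66 | 1.99 | 88% | 87% |
| 20% at zero change, mean changes 1.04 and −1.04 | 1.66 | 1.95 | 89% | 88% |

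The columns should be compared within themselves. A standardised difference of 0.977 gives 90% at 22 per group on the normal scale but 88.6% on the t scale. The constant-SD loss is thus 90 to 83 (normal) or 88.6 to 82 (t).

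**5. How much early dropout is tolerable.** At constant SD on the normal scale, 90% holds while (1 − q)² × 28 ≥ 22, that is q ≤ 1 − √(22/28) = 0.114. On the t scale, power at q = 0.10 is just under 90%. With mean changes of 9.50 and 7.42, power (t) is already 74% at 5% dropout and 56% at 10%.

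**The case against.** Four objections carry weight.

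- **Timing and balance.** The 20% has no time point, and the trial runs to week 8. Loss after week 4 does not touch the primary outcome. Unequal loss between arms could widen or narrow the difference. This stands: the figures are conditional on 20% lost before week 4 in both arms.
- **82% as a ceiling.** A reader might infer that power is at most 82%, because zeros mixed with real changes must widen the spread. The documents do not support that. The variance 0.8 × SD² + 0.16 × m² exceeds SD² only when m is above √1.25 ≈ 1.12 SD. With smaller mean changes the spread narrows and power is 87% to 88% (t).
- **A general failure of n/(1 − d).** A reader might also infer that any n inflated this way must miss its target under LOCF. That is too strong. If mean changes are near zero, the variance falls to 0.8 × SD², and (n/0.8) × 0.8²/0.8 = n, so nothing is lost. With the printed sigmas taken as SDs, 353/0.8 = 441.25, so 442 per group. Power with 20% zeros is then 89.8% for mean changes of 2.08 and 0, 89.2% for 4 and 1.92, and 84.1% for 9.50 and 7.42.
- **The larger fault lies elsewhere.** On the printed inputs the 90% is unsupported even with full follow-up. This stands, and it sets the order of correction. It does not remove the mismatch: someone who repaired only the sigmas would still have an allowance built for a different analysis.

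The division itself is correct and is a routine planning step. The fault is that it is paired with an analysis it does not describe.

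**Conclusion.** The mismatch is real and lies in the article's own text, so it is not a detail left to an unseen analysis plan. Granting 22 per group at 90%, and with the full 20% lost before week 4 equally by arm, every case computed falls below 90%. Power is about 82% (t) or 83% (normal) at constant SD, with a range on the t scale from about 35% if 9.50 and 7.42 are mean changes to about 88% if mean changes are small.

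The size of the loss is uncertain. It rests on a back-solved SD of 2.13, on mean changes that the article does not clearly give, and on dropout timing that it does not state. At constant SD, 90% is roughly kept if about 10% or fewer leave before week 4. The point is secondary to the error in the base calculation.

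**What to change.** 1. Correct the base calculation first. State the SDs of the change and the mean changes separately, and give the size or power that follows. Every dropout figure depends on these.
2. Then choose one of two routes:
   - Treat dropouts as missing in Statistical analysis, using a likelihood-based model or multiple imputation on the randomised set in place of LOCF. Dividing by (1 − d) is consistent with this.
   - Keep intention to treat with LOCF, and restate in Sample size the power of 28 per group under that analysis. Give the assumed dropout before week 4, the SD and the mean changes.
3. Use the same dropout assumption, with its timing, in both sections.

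The cost of this point is one recalculation and a few sentences, with no added patients. The first route changes the imputation method and should be settled before the unblinding that precedes analysis. The second probably means printing a lower power.

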### Recruitment

The researchers will distribute trial information leaflets to the inpatient and outpatient clinics of the hospital. Posters will also be used of recruitment. Suitable participants will be encouraged to ask a question about the study and given time to decide if they wish to participate. Participants who are willing to participate will be asked to provide written consent.

### Allocation

#### Sequence generation

Participants will be randomly allocated to either the acupuncture group or the control group in a 1:1 ratio by simple randomization. The randomization schedule was calculated in the statistical software SPSS (IBM SPSS statistics version 22.0, USA) by a statistical expert from the Faculty of Medical Statistics and Epidemiology, The Second Affiliated Hospital of Guangzhou University of Chinese Medicine.

#### Allocation concealment mechanism and implementation

The allocation sequences are enclosed in sealed envelopes with a unique identification number. The envelope will be sent to an investigator in charge of the group assignments. The investigator will specify in the envelope who and when to open the randomly assigned envelope. The number will appear on all report forms to maintain participant confidentiality.

#### Blinding

The acupuncturists are not blinded to group allocation. Participants are blinded to their group allocation but are informed that they had an equal chance of allocation to the acupuncture or control group before study participation. The outcome assessor will also be blinded to group allocation. Adverse reactions are carefully observed, and emergency unblinding is required if serious adverse reactions occur. Unblinding will be performed at the end of the trial to perform statistical analysis.

#### Data collection methods

Before study initiation, all researchers and acupuncturists will participate in a 2-day training session including assessment and collection of outcome, baseline, and follow-up organized by the Secondary Medical College of Guangzhou University of Traditional Chinese Medicine. During the follow-up period, participants are requested to return to the clinic to receive assessment and will be given subsidies to cover transportation. If the participants could not complete the entire study, and lost to follow-up, these data will be included in the statistics and should be analyzed intentionally.

#### Data management

The data and safety monitoring committee are composed of independent clinicians and biostatisticians with rich experience in clinical trials. The ethics committee of the Secondary Medical College of Guangzhou University of Traditional Chinese Medicine will perform random audits to ensure compliance with relevant regulations and guidelines. Any changes of the research protocol will be communicated to both the ethics committee and registration center timely. The case report form (CRF) is a paper version and should be properly recorded by the investigator. One researcher will be responsible for collecting data at each stage of the study, while another researcher will input the data into the SPSS software. This process will be carried out under the supervision of project monitors. According to the terms of informed consent, unless the subject’s consent is obtained, all the subject’s personal information is confidential and will not be disclosed to the public. The sponsor should keep CRF for 5 years after the end of the research.

### Statistical analysis

Descriptive statistics will be used to describe demographic data of sample groups, while the normality of the distribution of each parameter will be checked by histogram and the Kolmogorov-Smirnov test. The continuous variables will be presented in mean and standard deviation (SD). A chi-squared test will be used to assess sample characteristics and gender. The data that conform to normal distribution will be analyzed by one-way analysis of variance, while the nonconforming data will be analyzed by Mann-Whitney *U* test. The latency and amplitude of the ERP data will be analyzed by mixed-effect model analysis, the Greenhouse-Geisser adjustment will be applied to adjust the degrees of freedom if the assumption of Mauchly’s test of sphericity is not significant. *P* < 0.05 will be taken as the standard for a significant difference. Data analysis will follow the intention-to-treat principle including participants who are randomly assigned. Missing data will be input with the last observation carried forward method.

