### Outcome measures

The endpoints will be evaluated at baseline (before intervention), week 4 (immediately after intervention), and week 8 (1-month follow-up). We include two figures to show the participant timeline more clearly (see Figs. 1 and 2).

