#### Secondary outcomes

The secondary outcomes include the Wisconsin Card Sorting Test (WCST) and the latency and amplitude of the ERP components P1, N170, and P3 at week 4.
The WCST [24] is being adopted to assess cognitive function. Participants are required to match response cards to the four stimulus cards along one of the three dimensions (color, form, or number) by pressing one of the 1 to 4 number keys on the computer keyboard. The measured variables include categories completed (CC), total errors (TE), perseverative errors (PE), and nonperseverative errors (NRPE).ERP

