##### Stimuli

Facial pictures are grayscale photographs selected from the native Chinese Facial Affective Picture System [16], and a total of 60 facial pictures are used as target faces (20 happy, 20 neutral, and 20 fear faces) with an equal number of males and females. Each picture was assessed for its valence and arousal on a 9-point scale with a large sample of Chinese participants in a previous survey. Each pair of facial stimuli will consist of a neutral picture and an emotional picture. Thus, we will have pairs of emotional-face stimuli consisting of 60 emotional faces, including 20 happy-neutral, 20 sad-neutral, and 20 fear-neutral pairs of facial stimuli.

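### The Greenhouse-Geisser rule for the ERP data is stated backwards; followed literally in a repeated-measures ANOVA, it lets nominal 5% tests on the three-level emotion factor run at up to about 8%

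*Protocol article*

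**What the plan says.** The rule stands in the Statistical analysis section of the protocol article. The method for the ERP outcomes is named first: "The latency and amplitude of the ERP data will be analyzed by mixed-effect model analysis". The same sentence then adds that "the Greenhouse-Geisser adjustment will be applied to adjust the degrees of freedom if the assumption of Mauchly’s test of sphericity is not significant". The significance level is P "< 0.05 will be taken as the standard for a significant difference". No other section restates or corrects the rule.

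Three other places show what the rule would act on:

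- Stimuli: the face cues form three emotion conditions, "20 happy-neutral, 20 sad-neutral, and 20 fear-neutral pairs of facial stimuli".
- Outcome measures: endpoints are assessed at "baseline (before intervention), week 4 (immediately after intervention), and week 8 (1-month follow-up").
- Secondary outcomes: the ERP endpoints are "the latency and amplitude of the ERP components P1, N170, and P3 at week 4".

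**The concern.** Mauchly's test takes sphericity as its null hypothesis. A significant result is evidence that sphericity fails, and that is when the univariate F test needs reduced degrees of freedom. A non-significant result gives no such evidence. The article attaches the correction to the non-significant result and so removes it where it is needed.

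An uncorrected F test on a non-spherical factor rejects a true null hypothesis too often. The trial hypothesises an effect of acupuncture on negative emotion processing bias. The natural test of that in the ERP data is whether the response to the emotion categories differs by group, which is a group by within-subject interaction on a factor with more than two levels. This is the kind of test the rule governs.

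The sentence also combines two frameworks. Mauchly's test and the Greenhouse-Geisser correction belong to repeated-measures ANOVA. A likelihood-based mixed-effects model handles the within-subject covariance through the structure specified for it and has no place for this step.

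**Working it through.** The article gives no figure for this rule, so there is nothing to reproduce. The check has two parts: the logic of the rule, and a simulation of its error rate.

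**1. Logic**

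| Mauchly's test | Meaning | Usual action | Action in the article |
|---|---|---|---|
| P ≥ 0.05 | sphericity not rejected | no correction needed | correct |
| P < 0.05 | sphericity rejected | correct | no correction |

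Both rows are reversed.

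**2. Inputs for the simulation**

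- Alpha 0.05 (Statistical analysis).
- k = 3 emotion conditions (Stimuli).
- 28 per arm: "the total number of patients required for this trial was 56, with 28 in each group" (Sample size). The plan analyses by intention to treat with last observation carried forward, so 28 is the main case.
- 22 per arm as a completers case, from the 20% dropout in Sample size: 28 × (1 − 0.20) = 22.4.
- Within-subject covariance: not given. Assumption: four 3 × 3 matrices with epsilon from 1.00 to 0.55. The lowest possible value for three levels is 1/(k − 1) = 0.50.

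**3. Formulas**

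Let p = k − 1 and v = 2n − 2, let C be the orthonormal contrasts, Σ the within-subject covariance matrix, and V = CΣCᵀ.

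- Epsilon = (tr V)² / (p · tr V²).
- Uncorrected interaction test: F on p and p·v degrees of freedom. For n = 28 this is 2 and 2 × 54 = 108. For n = 22 it is 2 and 2 × 42 = 84.
- Corrected test: both degrees of freedom multiplied by the estimated epsilon.
- Rule as written: corrected P value if Mauchly P ≥ 0.05, otherwise uncorrected.
- Rule reversed: corrected P value if Mauchly P < 0.05, otherwise uncorrected.

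Example of epsilon: with unit variances and correlations 0.95, 0.2 and 0.2, V is diagonal with entries 1 − 0.95 = 0.05 and (6 + 1.9 − 0.8 − 0.8)/6 = 1.05. So epsilon = (1.10)² / (2 × (0.0025 + 1.1025)) = 1.21/2.21 = 0.548.

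**4. Results**

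Type I error of the group by emotion test under the null hypothesis, 20,000 simulated trials per row. The simulation standard error at 5% is √(0.05 × 0.95/20,000) = 0.0015, or 0.15 percentage points.

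| n per arm | Assumed covariance | Epsilon | Mauchly significant | As written | Reversed | Always corrected |
|---|---|---|---|---|---|---|
| 28 | equal variances, correlation 0.5 | 1.00 | 5.1% | 4.7% | 4.9% | 4.7% |
| 28 | autoregressive, 0.8 | 0.85 | 83.6% | 5.9% | 5.1% | 5.1% |
| 28 | SDs 1, 1, 2; correlation 0.5 | 0.75 | 99.3% | 6.1% | 4.8% | 4.8% |
| 28 | correlations 0.95, 0.2, 0.2 | 0.55 | 100% | 7.8% | 5.1% | 5.1% |
| 22 | equal variances, correlation 0.5 | 1.00 | 4.9% | 4.9% | 5.1% | 4.9% |
| 22 | autoregressive, 0.8 | 0.85 | 72.4% | 5.4% | 4.8% | 4.6% |
| 22 | SDs 1, 1, 2; correlation 0.5 | 0.75 | 96.6% | 6.7% | 5.3% | 5.3% |
| 22 | correlations 0.95, 0.2, 0.2 | 0.55 | 100% | 8.1% | 5.0% | 5.0% |

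A second set of runs (10,000 per scenario, 22 or 28 per arm) agrees. The rule as written gave 4.3–4.7% at epsilon 1.0, about 5.6% at 0.86, 6.3% at 0.75 and 7.6–7.9% at 0.62–0.55. The reversed rule gave 4.4–5.2%.

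Once Mauchly's test has high power, the rule as written gives the same error rate as no correction at all (7.8% under both at epsilon 0.55 and n = 28). When sphericity holds, the rule as written and the reversed rule differ by 0.2 percentage points.

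**The case against.** The strongest reply is that this is a slip of language. An assumption is met or not met; it is not significant. The clause looks like a merger of two correct phrasings, one about an unmet assumption and one about a significant test, and the article has other language slips. An experienced analyst would probably apply the correction the right way round. That lowers the severity but does not remove the point. A prespecified rule is taken as it reads, nothing else in the article repairs it, and this is a wrong statement rather than detail left to a fuller document.

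The second reply is that the article names a mixed-effect model. If a likelihood-based model is fitted, the clause never operates and none of the inflation arises. This stands, and it makes every figure above conditional on a mixed-design repeated-measures ANOVA. The article does not settle which is meant, and the sentence needs rewriting on either reading.

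The third reply concerns scope, and it also stands. The ERP outcome is set at week 4. Baseline versus week 4 is a two-level factor, on which sphericity cannot fail. Only effects on within-subject factors with three or more levels, and their interactions with group, are exposed. Emotion is such a factor; visit would be one only if week 8 enters the ERP model.

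A reader might go further and infer error rates near or above 10%. Simulations with more cells do reach that: 8.3% for six cells (epsilon 0.56) and 11.3% to 13.2% for nine cells (epsilon 0.36 to 0.23), at 28 per arm. The article does not support using these figures for this trial. It states no six- or nine-level factor, and it describes the 64-electrode cap as recording equipment, not as a factor in the analysis. A reader might also infer a material loss of power where sphericity holds, but the results at epsilon 1.00 show almost no effect.

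**Conclusion.** The rule is stated backwards, and the sentence should be corrected. For the three-level emotion factor, literal use in a repeated-measures ANOVA gives a type I error of about 5% with no violation, about 6% at epsilon 0.85 to 0.75, and up to about 8% at 0.55, against a nominal 5%. The reversed rule holds 4.8% to 5.3% in the scenarios tabulated.

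This rests on three conditions: the analysis is a mixed-design ANOVA, the text is followed as printed, and the true epsilon lies in the assumed range. The article gives no covariance from which to check the last.

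It would be tempting to conclude that the trial's ERP error rates are wrong, or that its main result is at risk. Neither follows. The first depends on the three conditions above. The second fails because the HAMD-17 primary analysis, the group main effects and any two-level comparison do not pass through this rule. Severity is moderate and limited to secondary endpoints.

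**What to change.** Decide which analysis is meant and rewrite the sentence to match.

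- If it is a mixed-design repeated-measures ANOVA: state that the Greenhouse-Geisser correction is applied when Mauchly's test is significant (P<0.05). Alternatively, state that it is always applied to within-subject factors with more than two levels. Always correcting gave 4.6% to 5.3% in the table above and avoids making the correction depend on a preliminary test.
- If it is a likelihood-based mixed-effects model: delete the Mauchly and Greenhouse-Geisser clause. The covariance structure can be left to the analysis plan.

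The cost is one sentence. Sample size, data collection and the primary analysis do not change. The correction should be on record before the ERP data are analysed, so that the choice is not made with results in view.
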